**Figure 1 ztaf004-F1:**
[figure not shown]
During the CONAN study, clinical congestion assessment will be conducted at study visits. These procedures will be consistently repeated at each visit. Subsequently, clinical endpoints will be evaluated.

The baseline visit of a given patient will be conducted within the initial 24 h after diagnosis of ADHF. During the baseline visit, the following data will be obtained: medical history including HF entity, comorbidities, symptoms, signs, vital signs, laboratory values, and bioelectrical impedance analysis (*Table 2*). Bioelectrical impedance analysis will be performed by clinical staff to assess the patient’s total body water composition. Additionally, the EVEREST Score will be computed that serves as an established clinical tool for assessing congestion in patients with HF. The score scales rate congestion severity, utilizing clinical parameters such as dyspnoea, orthopnoea, oedema, and jugular venous pressure.^18^ Three paper-based validated questionnaires will be used to assess digital health literacy (HLS_19_-DIGI) overall, self-care behaviour in HF using the nine-item European Heart Failure Self-care Behaviour Scale (EHFScB-9), and the Kansas City Cardiomyopathy Questionnaire (KCCQ-12), which assesses the quality of life in patients with HF.

**Table 2 ztaf004-T2:** Study procedures during the CONAN study

Procedures	Baseline (V_Baseline_) Confirmed ADHF Day 0/+24 h	Visit a (V_a_) In the case of inpatient treatment, the day of discharge	Visit 1 (V_1_) Regular outpatient visit Day +14 days (±7 days)	Visit *n* (V*_n_*) Any unplanned clinic visit (i.e. ER visit) Day +*n*	Visit end-of-study (V_EOS_) Regular outpatient visit Day +90 days ± 14 days
Inclusion/exclusion criteria	X				
Demographics	X				
Past medical history incl. HF entity	X				
Concomitant medication	X	X	X	X	
Vital signs and body weight	X	X	X	X	X
HLS_19_-DIGI	X				
Kansas City Cardiomyopathy Questionnaire (KCCQ-12)	X				X
European Heart Failure Self-care Behaviour Scale (EHFScB-9)	X				X
Safety/Deficiencies Assessment		X	X	X	
EVEREST Score^18^	X	X	X	X	X
Mobile Application Rating Scale (MARS-G)^19^					X
System Usability Scale (SUS)					X
Bioelectrical impedance	X	X	X	X	X
Parameters using the *monti* platform					
Connection attempts to the server		X	X	X	X
Number of daily ECG recordings		X		X	X
Completed uploads including timestamp and file size		X	X	X	X
Failed uploads		X	X		X
Completeness of vital signs and physical activity time-series data:		X	X		X
Number of notifications and type (e.g. reactivate/charging)		X	X		X
Number and type of contacts (e.g. phone call for technical support)					X

During follow-up visits, symptoms, signs, and vital signs will be assessed. As part of the safety assessments, local skin reactions or discomfort are monitored, and the technical equipment is inspected for any obvious damage. Moreover, details regarding HF hospitalizations and all unplanned, non-trauma-related hospitalizations and emergency department visits will be recorded. During the visit at 14 days post-discharge, the first 10 patients will complete the System Usability Scale (SUS) to identify any potential deficits in the monitoring platform that can be iteratively optimized. The SUS measures the overall usability of a system by capturing user perceptions of its ease of use and learnability. As there are multiple translations to German, the version of Rummel *et al*. was chosen.^20^

The end-of-study visit will be scheduled on Day 90 post-initial discharge, with a window of plus or minus 14 days. EHFScB-9 and KCCQ-12 questionnaires are completed by the patients again. Additionally, the SUS and Mobile App Rating Scale (MARS-G) questionnaires will be handed out to the patients. These are validated tools used to assess the quality and usability of digital health applications.^19^ MARS-G evaluates various aspects of mobile app performance, including engagement, functionality, aesthetics, and information quality. In the event of withdrawal of consent, patients will be asked to complete an end-of-study visit at the earliest possible date.

### Wearable-based monitoring platform

We developed ‘monti’ a platform that continuously records vital and activity parameters in near real-time using a non-invasive wearable, securely transmits the data, and analyses it with self-learning artificial intelligence. Enrolled patients will receive a registered smartphone and the CardioWatch 287-2 wrist-wearable (Corsano Health B.B., [name]). The smartphone will function both as a wearable data proxy and a user interface for the assessment of electronic patient-reported outcomes (ePRO) via a smartphone application. The commercially available wearable employed is a CE-marked medium-risk device (class IIa) according to Directive 93/42/EEC.^21^ Various sensors integrated into this wearable device are utilized for monitoring vital signs and physical activity, including photoplethysmography, temperature probe, and accelerometer (*Table 3*). The electrocardiogram (ECG) sensor necessitates active patient engagement, with patients requested to record a 30 s ECG once daily. Patients will be instructed to charge the wearable every other day for ∼90 min. Additionally, a brief patient manual with key information and contact will be provided. With the app, patients can record ePRO regarding their subjective symptoms in a concise symptom inventory. The app also includes a feature for users to concisely record self-measured parameters such as body weight, blood pressure, pulse rate, and body temperature as a diary function. The recorded values are displayed in a tabular format within the app, incentivizing users to actively engage with the app.

**Table 3 ztaf004-T3:** Vital signs and physical activity parameters that will be recorded with the wearable

Parameter	Frequency	Unit
Raw photoplethysmography data (green, red, infra-red light)	32 Hz (up to 128 Hz)	
Heart rate	1/10 s	Beats per minute
Steps	1/10 s	Step count
Calories	1/10 s	
Core body temperature	1/10 s	°C
Respiration	1/10 s	Breath rate per minute (BRPM)
Peripheral oxygen saturation (SpO_2_)	1/10 s	%
RR intervals	1/s	ms
Sleep	1/30 s at nights	Categorical (1 = awake, 2 = rem, 3 = light, 4 = deep)
Bio impedance (BioZ)^a^	25 Hz	
ECG		No unit

^a^Explorative analysis only.

All study equipment will be collected at the end-of-study visit. In the event that no data is received from an enrolled patient for 1 day, the patient is reminded via a push notification to use the monitoring system. If no data is received for 2 consecutive days, the patient is contacted by phone to determine whether there is a technical problem. If the patient wishes to terminate the study, he will be excluded and asked to return the devices at the next regular visit to the study site. If this is not possible, the study team can offer to collect the devices at the patient’s home. If a patient is lost to follow-up, he will be contacted during the next regular visit to the study site to return the equipment.

### Data collection

Wearable data and ePRO data will be transmitted by monti via mobile data services to a centralized server that runs real-time data analysis and analysis software. The data recorded by the wearable will include time-series data of raw signals as well as vital signs and physical activity parameters, with the latter computed using proprietary algorithms provided by the manufacturer. Vital signs and physical activity parameters, such as heart rate, temperature, respiratory rate, and physical activity, will be recorded at a rate of up to 1 Hz. Thus, up to 3600 data points are potentially generated per hour, each paired by a corresponding quality index. On the platform backend, data integrity is assessed by monitoring actual wearing time, both initial and ongoing app usage, and overall data quality. Data integrity assessments are conducted at interim study visits and the study’s conclusion (*Table 2*).

Clinical records (visit entries, laboratory results, diagnostic results) will be documented in worksheets. Records will be independently and retrospectively reviewed by two cardiologists for the presence of ADHF. Worksheet entries and results of the validated questionnaires are transferred into a database.

Time-series data recorded by the wearable will be annotated based on clinical records. At each follow-up visit, where a clinical congestion assessment is conducted, the 2 days prior and post-visit are annotated as either ADHF or regular, as determined by the congestion assessment on the visit day.

Exploratively, the dataset of regular episodes may be enriched by including episodes beyond this initial 2-day window if patients report stable symptoms and vital signs through the app. This approach allows for the evaluation of whether these additional episodes show consistent ‘regular’ patterns suitable for model training. Datasets will be split into hours according to their timestamps, and only hours with a >90% amount of data points will be included to ensure sufficient information content among hours. No predefined quality constraints are used.

To calculate the risk index, ‘regular’ hours collected during the study are used to train a deep neural network with a self-supervised contrastive learning objective, extracting features typical of regular periods. Training and test data are split 90/10. The model is used to calculate a risk index that measures the dissimilarity to regular features. The detection and predictive performance of the risk index will be compared to clinical documentation of ADHF. To evaluate the risk index’s predictive capabilities over time, the timestamp of the clinical ADHF diagnosis will be used as a reference point. The risk index computed by the model will subsequently be examined for the days preceding an ADHF event. This analysis aims to identify early deviations in the risk index that could potentially be driven by subclinical changes in physical activity or vital sign patterns.

Data collection will be conducted following an intention-to-treat approach and will continue until withdrawal, except in cases where there is a specific request to delete all individually recorded data.

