### Study procedures

In- and outpatients with ADHF will consecutively be screened for in- and exclusion criteria at the cardiology department at University Hospital RWTH Aachen (*Figure 1*). All patients will be treated according to the standard of care, and the study visits will be scheduled accordingly. The monitoring period starts from the inclusion of the patients into the study followed by continuous monitoring of vital signs and physical activity by the wearable for 90 days. Based on the decision by the treating physician eligible patients will be admitted for treatment to the study site or will be treated as outpatients. Follow-up visits are conducted on the day of discharge and in accordance with the guideline-based follow-up recommendations for patients experiencing ADHF, routine outpatient visits at the HF clinic will be scheduled ∼14 and 90 days post-discharge. If the patient initially receives inpatient treatment, the day of discharge and any unplanned visit to the outpatient clinic of the study site will be documented as study visits.

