### Statistical analysis

The sample size calculation was based on a 20% incidence rate of congestion, an 85% detection sensitivity of the risk index (see below), a 15% dropout rate, a 10% error tolerance, and a significance level of 0.05, indicating a need for ∼282 patients to achieve sufficient statistical power.

For statistical analysis differences between means of hours annotated as ‘regular’ and ‘congested’ obtained from risk score will be tested for significance using a two-sided *t*-test test, adjustment for multiple comparisons is performed by using Bonferroni correction. To address overfitting, a 10-fold cross-validation will be performed. Statistical significance will be tested by an analysis of variance within the cross-validation splits of ADHF and regular. Receiver operating characteristics analysis [area under the curve of the ROC-analysis (AUROC)] will be computed to assess the primary endpoint. The cut-point that optimizes the detection of true positive results (sensitivity) and false positive results (1-specificity) is reported by the Youden index. For clinical requirements (not missing an event), specificity will additionally be reported at a sensitivity of ∼95%.

To assess risk score prediction capabilities for congestion detection, the performance of the score up to 7 days before and after the timestamp of diagnosis (t = 0 h) will be analysed. For AUROC-analysis, 95% confidence intervals are reported. A *P*-value of <0.05 will be considered significant. For data and statistical analysis, an open-source software tool will be used.

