## Discussion

By performing this prospective observational cohort pilot study, we aim to assess the functionality and usability of a passive monitoring platform to detect ADHF in a cohort of patients with a history of ADHF for a duration of up to 3 months.

The primary outcome of this study is to assess the accuracy of a risk index in detecting ADHF. To account for individual variations in vital signs and physical activity, our self-supervised contrastive learning-derived risk index aims to detect divergence from a regular episode in the multiple parameters recorded, instead of focusing on a single parameter with rigid thresholds. A prerequisite for achieving high detection rates with this approach is the availability of a robust dataset of ‘regular’ episodes that enables reliable pattern recognition from wearable-recorded vital signs and physical activity parameters.

To support this, we defined a 2-day window around study visits for the annotation of regular episodes, ensuring a substantial dataset for training. Given the close temporal proximity of this window, significant differences in congestion state are considered unlikely. Additionally, the model must capture temporal patterns of wearable-recorded parameters under varying conditions, such as rest and physical activity, and in diverse settings, including inpatient and outpatient contexts. Achieving comprehensive coverage of these patterns—referred to as ergodicity—is anticipated to enhance the accuracy of ADHF detection. Conversely, insufficient ergodicity during these periods may diminish the informativeness of the risk index, potentially leading to an increased rate of false positives.

An exploratory approach will involve extending the ‘regular’ dataset by including episodes beyond the 2-day window, contingent upon patients reporting stability in symptoms and vital signs via the app. This evaluation aims to determine whether such episodes show consistent patterns that can enrich the dataset and improve ergodicity.

Furthermore, we will investigate the use of pre-trained neural networks, commonly referred to as Foundation Models, which are designed for specific applications such as image recognition. These models may optimize the pattern recognition of regular episodes, potentially reducing the amount of data required for effective training.^22^

By comparing against different congestion assessment tools, the performance and robustness of our risk index will be assessed.

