## Conclusion

In conclusion, this pilot study aims to evaluate the following key aspects to consider before a potential integration of a remote monitoring platform into a clinical care pathway.

First, the efficacy and safety of the monitoring platform in the pre-emptive detection of congestive episodes among a large cohort of patients with HF will be evaluated.

Secondly, a patient perspective is added through quality assessment of the app using the SUS questionnaire conducted under real-world conditions, as it is pivotal for the development of a widely applicable digital tool in HF management. This holistic approach will enhance technical understanding and is essential for the subsequent seamless integration into the clinical routine.

Thirdly, a successful risk index in the context of heart failure may serve as a valuable tool throughout the patient journey to monitor aspects such as treatment success.

This study will analyse the entire process, from data recording to the provision of a risk index for the detection of ADHF in patients with a history of ADHF as actionable information including technical and human factors.

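### As planned, AUROC and specificity rest on hours within 2 days of a follow-up visit, about 4–17% of the 90 monitored days, and so do not show the alert burden of continuous monitoring

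*Protocol article*

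**What the plan says.** Study procedures plans "continuous monitoring of vital signs and physical activity by the wearable for 90 days", starting at inclusion. Visits are sparse: "routine outpatient visits at the HF clinic will be scheduled ∼14 and 90 days post-discharge". In addition, for patients first treated as inpatients, "the day of discharge and any unplanned visit to the outpatient clinic of the study site will be documented as study visits".

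Data collection sets the reference label at each follow-up visit: "the 2 days prior and post-visit are annotated as either ADHF or regular, as determined by the congestion assessment on the visit day". Hours labelled regular train the network, with a 90/10 split of training and test data. Statistical analysis adds 10-fold cross-validation.

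The accuracy measures are AUROC (primary, Table 4) and the Youden cut-point. Beyond that, "specificity will additionally be reported at a sensitivity of" about 95%.

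Two analyses reach outside the 2-day windows. One follows the score for up to 7 days either side of an ADHF diagnosis. The other is exploratory objective 5, which may add regular episodes from times when patients report stability in the app. Its accuracy measure in Table 4 is AUROC after the training data have been expanded. Table 4 lists no alert rate over monitored time.

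**The concern.** A specificity applies to the hours on which it was measured. Here the regular hours that train the model and the regular hours that test it come from the same kind of window, next to a clinic visit. With visits at about day 14 and day 90 after discharge, the stretch from roughly day 16 to day 88 has no label unless an unplanned visit falls in it. That is the time in which a continuous monitor would mostly run.

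The Discussion names the risk itself: "insufficient ergodicity during these periods may diminish the informativeness of the risk index, potentially leading to an increased rate of false positives". A test set drawn from those same periods cannot tell whether they cover everyday conditions well enough. The Conclusion nevertheless says that the study will evaluate "the efficacy and safety of the monitoring platform in the pre-emptive detection of congestive episodes". If the index alerts more often between visits than around them, the planned figures will not show it, and readers may take the visit-window specificity for the false-alarm rate in daily use.

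**Working it through.** The article gives no figure for the labelled share of monitored time, so there is none to reproduce. The share follows from the schedule.

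**Inputs**
- Recording: 90 days (Study procedures), used as the denominator throughout.
- Label window: 2 days before and 2 days after a visit, so 4 days, or 5 if the visit day is counted separately (Data collection).
- Scheduled follow-up visits: V1 and end of study (EOS) for outpatients; discharge, V1 and EOS for inpatients (Study procedures, Table 2).
- Device return: "All study equipment will be collected at the end-of-study visit", so the 2 days after EOS yield no data.
- Timing: EOS falls 90 ± 14 days after discharge, while recording is stated as 90 days from inclusion. The EOS window can therefore also lie after recording has ended.

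**Formula:** share = labelled days / 90.

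| Path | EOS window full | EOS cut at device return | EOS outside recording |
|---|---|---|---|
| Outpatient, 4-day window | 4+4 = 8 (8.9%) | 4+2 = 6 (6.7%) | 4 (4.4%) |
| Inpatient, 4-day window | 8+4 = 12 (13.3%) | 8+2 = 10 (11.1%) | 8 (8.9%) |
| Outpatient, 5-day window | 5+5 = 10 (11.1%) | 5+3 = 8 (8.9%) | 5 (5.6%) |
| Inpatient, 5-day window | 10+5 = 15 (16.7%) | 10+3 = 13 (14.4%) | 10 (11.1%) |

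The range is 4.4% to 16.7%. Even at the top, 75 of 90 days (83%) carry no label. Each unplanned visit whose window overlaps no other adds 4/90 = 4.4 to 5/90 = 5.6 percentage points. Windows rated ADHF contribute nothing to specificity, so for that measure these shares are upper limits.

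**What could be hidden (illustration; both specificities are assumptions).** Let specificity be 0.90 in the windows and 0.80 elsewhere, with labelled share w.
- Overall specificity = 0.90w + 0.80(1 − w).
- w = 0.044 gives 0.804, or 24 × 0.196 = 4.7 false-alert hours per day.
- w = 0.167 gives 0.817, or 24 × 0.183 = 4.4 hours per day.
- The plan would report 0.90, or 24 × 0.10 = 2.4 hours per day.

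If specificity is the same in and out of the windows, nothing is lost. The planned analysis would not show which case applies.

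**The case against.** The restriction is a defensible choice of reference standard. A label is given only near a clinical congestion assessment, records are reviewed by two cardiologists, and the Discussion argues that congestion state is unlikely to change within the window. Days without an assessment have no reference, so leaving them out of AUROC and specificity is correct. For outpatient visits the windows already include ordinary days at home, and nothing in the article shows that specificity is worse elsewhere. The primary outcome is discrimination of diagnosed episodes in a pilot, no false-alarm rate is promised, and an unseen analysis plan may add one.

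Most of this stands, and it rules out four stronger readings that a reader might infer:
- *The study cannot give an alert rate.* It can: the wearable records throughout, and hospitalizations and emergency visits are collected.
- *Nothing looks at the time between visits.* The analysis around diagnoses does so for up to 7 days. Objective 5 also asks whether between-visit episodes selected for reported stability look regular.
- *The Conclusion passes off visit-window specificity as monitoring performance.* It does not mention specificity.
- *Every unassessed day can be counted as a true non-event.* No reference supports this. Outpatients enter in confirmed ADHF, and the index is meant to pick up subclinical change.

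The objection does not remove the gap. The 7-day analysis is tied to events, and objective 5 is optional, selected on stability and scored through expanded training data. Neither gives an alert rate in ordinary time.

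**Conclusion.** The point holds for the primary analysis as the article describes it. AUROC and specificity describe hours near follow-up visits, about 4–17% of the 90 days for scheduled visits. The narrower 7–11% requires 4-day windows cut at device return and no unplanned visits. On every scheduled-visit reading at least 83% of the monitored days do not enter these measures, and the false-positive risk stated in the Discussion is left untested there.

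Whether specificity really is lower between visits is unknown, and the 2.4 versus 4.4–4.7 hours per day is only an illustration. The primary analysis is not invalid. What needs limiting is the conclusion drawn from it: visit-window specificity should not be read as the false-alarm rate of continuous monitoring.

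**What to change.** Keep the visit-window AUROC and specificity as the primary analysis and name them as visit-window measures. Add one descriptive secondary analysis:

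- Apply the index out of fold, with folds formed by patient, to all hours that meet the existing rule of more than 90% of data points, from the first visit rated regular to device return.
- Leave out the 7 days before and after any ADHF diagnosis.
- Report alert hours or days per patient-month at both planned cut-points (Youden, and about 95% sensitivity).
- Call the result an alert rate in time without a reference assessment, not a specificity.
- Base any statement about continuous or pre-emptive monitoring on this rate as well.

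The cost is analysis wording and computing time, since the recordings are already planned. The figure will probably look less favourable. Some alerts will reflect unrecognised or subclinical congestion, so the rate is an upper bound on false alarms in the scored time, by a margin that the study cannot quantify.

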**Methods and results:**

This is the protocol for a single-arm, prospective cohort pilot study that will include 290 patients with ADHF. Acute decompensated heart failure is diagnosed by clinical signs and symptoms, as well as additional diagnostics (e.g. NT-proBNP). Patients will receive standard-of-care treatment, supplemented by continuous wearable-based monitoring of vital signs and physical activity, and are followed for 90 days. During follow-up, study visits will be conducted and presentations without clinical ADHF will be referred to as ‘regular’ and data from these episodes will be presented to a deep neural network that is trained by a self-supervised contrastive learning objective to extract features from the time-series that are typical in regular periods. The model is used to calculate a risk index measuring the dissimilarity of observed features from those of regular periods. The primary outcome of this study will be the risk index’s accuracy in detecting episodes with ADHF. As secondary outcome data integrity and the score in the validated questionnaire System Usability Scale will be evaluated.

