### Participants

Inclusion criteria will be patients’ age ≥ 18 years with ADHF confirmed within the last 24 h. Acute decompensated HF is defined as worsening in dyspnoea at rest or with minimal activity, one or more accompanying signs (jugular venous pulsation ≥ 11 cm, hepatomegaly, peripheral oedema), and one or more objective measures of heart failure (six minute walking test < 200 m, N-terminal proBNP level ≥ 1000 pg/mL or a two-fold increase to baseline).^17^ Additionally, one of the following findings has to apply: chest X-ray (presence of pulmonary venous congestion or small pleural effusion) or vena cava imaging (one of two max. diameter > 2.2 cm and/or collapsibility < 50%) or lung ultrasound (more than three B-lines in more than two intercostal spaces bilaterally are considered diagnostic for the detection of interstitial and alveolar oedema). Exclusion criteria are defined as active malignant disease, pregnancy, active severe systemic infection (requiring intravenous antibiotic treatment), end-stage renal disease with dialysis, medical or mental conditions impairing the ability to continuously wear the wearable (e.g. dementia, skin abnormalities), and active implants, which might impair recordings (detailed inclusion and exclusion criteria are listed in *Table 1*).

**Table 1 ztaf004-T1:** Inclusion and exclusion criteria for the CONAN study

Inclusion criteria	Exclusion criteria
Clinically confirmed congestion within the last 24 h NYHA ≥ II Age ≥ 18 years and able to understand the design and objectives of the study Signed written informed consent and data safety agreement before any study-related activities Willingness to wear the wearable during the treatment period and return it on a follow-up visit	Active malignant disease Pregnancy Active severe systemic infection, defined as intravenous administration of antibiotics End-stage renal disease with dialysis Medical or mental conditions, such as dementia, that hinder the continuous use of the monitoring platform and associated equipment during the monitoring period Any condition that makes wearing the wearable device impossible (e.g. presence of a shunt, active bleeding, or absence of limbs) Mental incapacity or language barriers that preclude adequate understanding or cooperation, known or suspected not to comply with study directives or not to be reliable or trustworthy, or a subject who in the opinion of the investigator should not participate in the study

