### Outcome and objectives

The primary outcome of this pilot study with the monti platform will be the accuracy of detecting episodes with diagnosed ADHF by a self-supervised contrastive learning-derived risk index based on wearable-recorded time series assessed through *C*-statistics (*Table 4*). As a secondary outcome data integrity will be assessed through the percentage of wearable data per day, the time difference between logged time point of measurement and database, and the score in the SUS, will be evaluated. Additionally, several exploratory endpoints will be examined.

**Table 4 ztaf004-T4:** Objectives and outcome measures of the CONAN study

	Outcome measures
Primary objective	
Assess the capability of the self-supervised contrastive learning-derived risk index (from wearable-recorded time series) to detect episodes of acute decompensated heart failure (ADHF).	Area under the receiver operating characteristics (AUROC) curve for detecting episodes of diagnosed ADHF.
Secondary objective	
(2) Evaluate the data integrity of the *monti*-monitoring platform in terms of adherence, technical functionality, and data quality.	Adherence: Daily percentage of wearable data availability. Percentage of data availability over participation period. Availability of each parameter per day. Number of app-server connection attempts. Number of uploaded vital signs. Number of recorded ECGs. Number of dropouts. Technical functionality: Ratio of failed uploads to total uploads. Number/type of notifications sent via the app. Number/type of user contacts. Mean time difference between measurement and database logging. Data quality: Mean percentage of data with high quality indices determined by the wearable for each parameter per day.
(3) To assess usability of the mobile *monti* platform	Mean score on the System Usability Scale (SUS). Percentage of users rating the app as ‘easy to use.’
(4) Monitor adverse events, including device-related effects and deficiencies.	Number of skin reactions or discomfort. Number of observed device damages.
Explorative objective	
(5) Expansion of the dataset by including additional ‘regular’ episodes	Number of ‘regular’ episodes included for training, annotated based on the 2-day window of study visits. Number of the additional ‘regular’ episodes included for training, annotated based on patient-reported stable symptoms and vital signs via the app. AUROC detecting episodes with diagnosed ADHF with expanded training data.

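### The optional app rule for extra regular training episodes asks only for patient-reported stability, so unresolved ADHF reported as stable can be labelled regular in the objective 5 analysis

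*Protocol article*

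**What the plan says.** Two rules in the protocol article can make a period regular.

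- **Visit rule.** The abstract says that "presentations without clinical ADHF will be referred to as" regular. Data collection applies this at each follow-up visit: "the 2 days prior and post-visit are annotated as either ADHF or regular, as determined by the congestion assessment on the visit day".
- **App rule.** Data collection continues: "Exploratively, the dataset of regular episodes may be enriched by including episodes", namely "episodes beyond this initial 2-day window if patients report stable symptoms and vital signs through the app". Table 4, objective 5, counts these additional training episodes as "annotated based on patient-reported stable symptoms and vital signs via the app" and reports an AUROC with the expanded training data. The Discussion repeats the condition: "contingent upon patients reporting stability in symptoms and vital signs via the app".

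Two other statements fix the patient's state when recording begins. Participants requires "ADHF confirmed within the last 24 h", and Study procedures says "The monitoring period starts from the inclusion of the patients into the study followed by continuous monitoring".

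**The concern.** The visit rule describes a state: a clinician looked for ADHF and did not find it. The app rule describes the course of symptoms and vital signs. A patient whose dyspnoea and oedema are unchanged from yesterday may be stable and still congested. The app rule names no clinical assessment as its anchor, and this cohort starts in ADHF.

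The regular hours train the network, and the risk index measures dissimilarity from what it learned. If congested hours are among them, congestion looks more normal to the model. The index in true ADHF would then be expected to fall, and with it the AUROC under objective 5. That objective is meant to show whether app-labelled episodes can enrich the training data, and contamination of this kind would blur the answer.

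**Working it through.** The plan gives no figure on this point. The check is a reading of the labelling rules, followed by a count of the time they leave open.

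**1. Which periods carry a clinical label?** Data collection labels windows around follow-up visits. Study procedures names these as discharge (for inpatients), about day 14, day 90 and any unplanned visit. Baseline is not among them. The time after inclusion therefore has no ADHF label to block the app rule until the first follow-up window opens. After a new ADHF diagnosis, only 2 days on each side are protected.

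**2. Is there another barrier?** Data collection says the approach allows an evaluation of whether the added episodes look consistently regular. Objective 8 correlates clinical assessments with the app's symptom inventory. Neither gives a criterion for excluding an episode.

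**3. Unlabelled hours before the first follow-up window.**

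- Outpatient, counting day 14 from inclusion: (14 − 2) × 24 = 288 h. With the ±7-day visit window: (7 − 2) × 24 = 120 h to (21 − 2) × 24 = 456 h.
- Inpatient with a stay of L days (L is assumed; the article gives none): (L − 2) × 24 = 72, 120 or 192 h for L = 5, 7 or 10.
- If baseline is also taken to carry a 2-day ADHF label, subtract 48 h: 240 h (72 to 408 h) for the outpatient; 24, 72 or 144 h for the inpatient.

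**4. Hours after a new ADHF that stays unresolved for r days** (r is assumed): (r − 2) × 24 = 120 or 192 h for r = 7 or 10. The visit label itself covers 4 × 24 = 96 h, or 5 × 24 = 120 h if the visit day is counted separately.

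**5. Scale of the app rule over 90 days, without unplanned visits.** Three visits label 13 to 15 days (3 × 5 = 15, or 13 if recording ends at the last visit). Two visits label about 8 days (2 × 5 − 2). The open time is 90 − 15 = 75 to 90 − 8 = 82 days, or about 5 to 10 times the visit-labelled time.

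**6. Illustration of contamination.** Let c be the share of app-labelled days that are congested, u the share of open days admitted, R the open days and V the visit-labelled days, all of the latter taken as regular. The congested share of the training set is R·u·c / (R·u + V). Both c and u are assumptions. The low column uses R = 75, V = 15, u = 0.25; the high column uses R = 82, V = 8, u = 1.

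| c | low | high |
|---|---|---|
| 2% | 1.1% | 1.8% |
| 5% | 2.8% | 4.6% |
| 10% | 5.6% | 9.1% |
| 20% | 11.1% | 18.2% |

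For c = 5%, high: 82 × 0.05 / 90 = 4.6%.

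**The case against.** The strongest reply is that the rule was meant more narrowly. The Discussion presents the 2-day window as the way regular episodes are annotated and then speaks of extending the regular dataset past it. On that reading, app-reported stability only prolongs a period around a visit already rated regular, and unresolved ADHF never qualifies. This may well be the intent, but the text does not make it binding: the window in Data collection carries both labels, and Table 4 names patient report as the only basis.

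Second, the article does not define stable, and the full protocol may do so. That is fair. Still, the article gives the same criterion in three places, each time without a condition on congestion.

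Third, whether the added episodes are suitable is the question being explored, and visit-labelled and app-labelled training episodes are counted separately. A fall in AUROC with the expanded data would be visible against the primary result. This stands, and it limits the harm. It does not show whether a fall came from app labelling as such or from admitting unresolved ADHF.

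Fourth, the open hours are not congested hours. Patients are under treatment, and one who is improving may not count as stable. An hour must also have more than 90% of its data points. This stands in full.

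**Conclusion.** The point holds in a limited form. As written, the optional exploratory rule leaves unresolved index or new ADHF eligible for the regular training set whenever the patient reports stability. This departs from the abstract's definition of regular. The expected direction is a lower risk index in true ADHF and a lower objective 5 AUROC; the size cannot be derived from the article.

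The figure of 288 h (120 to 456 h) is an upper bound on eligible hours per outpatient before the day-14 visit. The share admitted depends on how many patients report stability while congested, which the article does not give. The inpatient and post-diagnosis figures rest on assumed durations, and the contamination table on assumed shares.

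Three stronger conclusions might be inferred, and the document supports none of them:

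- That congested patients will be trained as normal. The text says the dataset may be enriched, so such hours can be labelled regular, not that they are.
- That the primary result is biased. The primary AUROC rests on the visit labels.
- That a lower AUROC would be wrongly blamed on app labelling in general. Nothing in the article says how such a result would be interpreted.

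**What to change.** In Data collection, and in Table 4 under objective 5, add one condition: *an app-labelled episode is admitted as regular only if the patient's most recent clinical congestion assessment was regular.* App-reported stability then only extends a period already shown to be regular. The condition keeps app labels out of the time from inclusion to the first regular assessment, and from any ADHF diagnosis to the next regular assessment. Visit windows keep the labels they already have.

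The cost is one sentence and the loss of some additional regular hours, including some that were truly free of congestion. No new data are needed, and the primary analysis does not change. The condition does not reach the run-up to a new ADHF after a regular visit: days 7 to 3 before a diagnosis lie outside the 2-day window but inside the planned 7-day look-back, and could still be admitted if reported as stable.
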